### 8.1.3 Subgroup analyses

Comparisons will include:

1. Males versus females
2. Age (6-11 versus 12-17 years)

3. SARS-CoV-2 antibody positive versus non-positive at baseline

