| 2                                  | 75                                                                                                                                                                                                                                                                                                                                                                                                                                                                                                                                                                                           |                                                       | ChAdOx1 nCoV-19 5.0 x10  vp (N=60) OR MenB (N=15) with homologous boost at D112 |       |   |     |          |   |    |             |                                                                                             |   |    |                                                                                              |   |    |            |                                                                                              |   |    |
| 3                                  | 56                                                                                                                                                                                                                                                                                                                                                                                                                                                                                                                                                                                           | 6-11 years                                            | ChAdOx1 nCoV-19 5.0 x10  vp (N=90) OR MenB (N=21) with homologous boost at D112 |       |   |     |          |   |    |             |                                                                                             |   |    |                                                                                              |   |    |            |                                                                                              |   |    |

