**Table 1b) SARS CoV-2 S-binding antibody response to ChAdOx1 nCoV-19**

| Dose interval | Baseline GMT (95% CI)      | 28 days after dose 1 (95% CI)        | 28 days after dose 2 (95% CI)           |
|---------------|----------------------------|--------------------------------------|-----------------------------------------|
| <6 weeks      | (N=481) 60.51 (54.1; 67.7) | N=479) 8,734.08 (7,883.1; 9,676.9)   | (N=443) 22,222.73 (20,360.50; 24,255.3) |
| 6-8 weeks     | (N=137) 58.02 (46.3; 72.6) | (N=99) 7,295.54 (5,857.4; 9,086.7)   | (N=116) 24,363.10 (20,088.5; 29,547.3)  |
| 9-11 weeks    | (N=110) 48.79 (39.6; 60.1) | (N=87) 7,492.98 (5,885.1; 9,540.2)   | (N=106) 34,754.10 (30,287.2; 39,879.8)  |
| >12 weeks     | (N=154) 52.98 (44.4; 63.2) | (N=152) 8,618.17 (7,195.4; 10,322.3) | (N=154) 63,181.59 (55,180.1; 72,343.4)  |

GMT: geometric mean titre, evaluated using multiplex immunoassay

COV006 will be the first time that ChAdOx1 nCoV-19 is administered to participants under the age of 18. However, ChAd vectored vaccines have previously been administered to over 400 children and adolescents aged 5-17 years of age [28] as well as children of younger ages, with acceptable safety and tolerability profiles; these children took part in clinical studies conducted by or in partnership with the University of Oxford in the UK and overseas (Table 2). ChAd vectored vaccines were given at doses ranging from  $2.5 \times 10^{10}$  to  $1.0 \times 10^{11}$  vp and no serious adverse reactions related to the vaccine were reported (Table 2).

Following the initial phase of recruitment of 6-11 year olds in this trial, and a review of the D7 diary card data in this population, the DSMB noted that the reactogenicity profile of the younger cohort might be higher than in the older age group and therefore safety bloods were warranted in a subset of this cohort.

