## 5. TRIAL DESIGN

This is a Phase II, single-blinded, -controlled, individually randomised study in healthy children and adolescents aged 6-17 years recruited in Oxford, Southampton, Bristol and London, of ChAdOx1 nCoV-19 or active control (licensed Meningococcal B vaccine) administered via an intramuscular injection into the deltoid muscle. The study will assess safety, tolerability and immunogenicity of ChAdOx1 nCoV-19.

Dose justification is discussed more extensively in section 8.4. Preliminary phase III trial data of ChAdOx1 nCoV-19 at  $5.0 \times 10^{10}$ vp /  $5.0 \times 10^{10}$ vp in adults aged 18 and over suggests a favourable safety, immunogenicity and efficacy profile [25]. Data on the use of adenovirus vectors in teenage cohorts is limited, however existing studies suggest an acceptable side effect profile at  $5.0 \times 10^{10}$ vp in teenagers (Table 2). Multiple studies have indicated that adverse side effects associated with adenovirus vectors increase with age de-escalation. Therefore, age de-escalation is being explored in this study. Published immunogenicity data explored D28 and D56 boosting intervals and ChAdOx1 nCoV-19 has been approved for use with a booster interval between 4 and 12 weeks. To bring the results of this trial in line with current policy on adult vaccination, to facilitate direct comparison with adult data should a paediatric vaccination programme be implemented, this study was initially intended to explore both 4 and 12 week booster intervals. Following the updated advice from the JCVI dated 8th April, and a subsequent review of safety data following booster dose administration in the UK adult population, a decision has been taken to boost all remaining children in the trial at a 16 week interval. This means that all children in Groups 2, 3 and 4 will be boosted at D112. There is no intention to recruit further participants into this study.

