**Table 3: Study groups**

| Group | N  | Age         | Schedule                                                                                     |
|-------|----|-------------|----------------------------------------------------------------------------------------------|
| 1     | 75 | 12-17 years | ChAdOx1 nCoV-19 $5.0 \times 10^{10}$ vp (N=60) OR MenB (N=15) with homologous boost at D28   |
| 2     | 75 |             | ChAdOx1 nCoV-19 $5.0 \times 10^{10}$ vp (N=60) OR MenB (N=15) with homologous boost at D112  |
| 3     | 56 | 6-11 years  | ChAdOx1 nCoV-19 $5.0 \times 10^{10}$ vp (N=44/46) or MenB homologous boost (N=10/11) at D112 |
| 4     | 55 |             |                                                                                              |

In both age groups, participants will be randomised 4:1:4:1 to receive ChAdOx1 nCoV-19  $5.0 \times 10^{10}$ vp/  $5.0 \times 10^{10}$ vp (boost at D28) or MenB/MenB (boost at D28) or ChAdOx1 nCoV-19  $5.0 \times 10^{10}$ vp/  $5.0 \times 10^{10}$ vp (boost at D112) or MenB/MenB (boost at D112). Due to the updated guidance by the MHRA and JCVI regarding the use of ChAdOx1 nCoV-19, all the 6-11 year olds children randomised to receive a D28 boost (group 3) will be boosted at D112.

Enrolment will begin with older participants aged 12-17 years in Groups 1&2 (150 participants, 120 of whom will receive the IMP. These 150 participants will be given their prime dose first. Safety and reactogenicity data from these 150 participants will be reviewed at D7 after the prime dose and reviewed by the CI, relevant investigators and the chair of DSMB and provided for review by the MHRA before age de-escalation with the recruitment of a sentinel group of the 6-11 year cohort (5 participants from Group 3 and 5 participants from Group 4) can take place. In particular, attention will be paid to whether safety and reactogenicity support proceeding with the same dose in younger children or whether dose de-escalation may be required. This D7 safety review will also allow boosting of the 150 participants in Groups 1 and 2.

Safety data from the sentinel group of 10 6-11 year olds will again be reviewed at D7 post-prime by the CI, relevant investigators and the chair of DSMB and again provided for review by the MHRA to allow enrolling and dosing of remaining participants.

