## 10. STATISTICS

### 10.1. Sample size

The total sample size of this trial will be 261 with 60 participants in ChAdOx1 nCoV-19 groups and 15 in each of the Meningococcal B vaccine groups for Groups 1 and 2. With a sample size of 60 participants, the probability of observing at least one participant with an adverse event will be more than 90%, if the underlying incident rate is 5%. The analysis for primary endpoints will be descriptive and there has been no formal power calculation to determine the sample size of the trial. The numbers have been therefore chosen based on practical constraints.

Following the updated safety guidance from the JCVI on 8th April 2021 [39], no more participants have been recruited. All the participant aged 6-11 years who randomised to group3 (boosted at 28 days) will be boosted at 112 days. The planned sample size of 75 has been achieved in Groups 1 and 2, and recruitment in Groups 3 and 4 stands at 55 and 56 respectively. As Groups 3 and 4 will both be boosted at D112 post prime, the two groups will be combined for all the safety and immunogenicity analysis. Therefore, the analysis of the younger age cohort will have increased power.

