### **10.4. The Level of Statistical Significance**

There will be no statistical significance testing for primary endpoints of safety. For secondary endpoints of immunogenicity, the level of significant will be two-sided 0.05.

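### The 6-11 versus 12-17 age comparison does not hold boost interval fixed, so a post-boost immunogenicity contrast of whole age bands would mix age with interval

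*Protocol*

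**What the plan says.** The subgroup list (numbered 8.1.3, within section 10 of the protocol) includes "Age (6-11 versus 12-17 years" with no restriction to, or stratification by, boost interval. Section 10.1.2 compares continuous immunogenicity data with a Mann-Whitney U test and seroconversion with a chi-squared test. Neither is adjusted. Section 10.4 adds: "For secondary endpoints of immunogenicity, the level of significant will be two-sided 0.05".

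The two age bands no longer share a schedule. Table 3 keeps Group 1 (12-17 years, 60 ChAdOx1 nCoV-19 and 15 MenB) "with homologous boost at D28". Section 5 says of the rest: "This means that all children in Groups 2, 3 and 4 will be boosted at D112". The synopsis gives the 6-11 year cohort as ("N=90) OR MenB (N=21) with homologous boost at D112"), where the 90 are ChAdOx1 nCoV-19 recipients.

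Section 10.1 took account of the change for the younger cohort only. Because Groups 3 and 4 now share a day 112 boost, "the two groups will be combined for all the safety and immunogenicity analysis". No such statement is made about Groups 1 and 2, and the subgroup list carries no matching revision.

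**The concern.** Under the 4:1:4:1 randomisation in both age groups, each band would have contained equal numbers at each interval, so comparing whole bands would have been balanced on interval. Moving Group 3 to day 112 removed that balance. Read plainly, 12-17 years means Groups 1 and 2 together, so half of one side has the short interval and none of the other side does.

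The protocol's own background data suggest that interval matters for post-boost antibody. In Table 1b the adult geometric mean titre 28 days after dose 2 is 22,222.73 for intervals under 6 weeks, and "63,181.59 (55,180.1; 72,343.4") for intervals over 12 weeks.

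At stake is whether younger children respond as well as adolescents after two doses. The error can run either way: an apparent advantage in younger children that is really the longer interval, or a weaker response in younger children offset by it. The second is arguably worse, because nothing in the result would prompt a reader to look further.

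**Working it through.** **The plan's own figures.** The protocol gives no figure for the age comparison. The one probability in section 10.1 reproduces: 1 − 0.95^60 = 95.4%, consistent with more than 90%. The total also reproduces: 75 + 75 + 56 + 55 = 261.

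**Inputs.**
- ChAdOx1 nCoV-19 recipients: 60 (Group 1, day 28), 60 (Group 2, day 112), 90 (Groups 3 and 4, day 112), from Table 3 and the synopsis.
- Adult titres 28 days after dose 2 (Table 1b): 22,222.73 (95% CI 20,360.50 to 24,255.3; N = 443) under 6 weeks; 63,181.59 (55,180.1 to 72,343.4; N = 154) over 12 weeks.
- Test: two-sided Mann-Whitney at 0.05.

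**Spread of titres.** SD of ln titre = ln(upper/lower) / (2 × 1.96) × √N.
- Under 6 weeks: ln(24,255.3/20,360.50) / 3.92 × √443 = 0.94.
- Over 12 weeks: ln(72,343.4/55,180.1) / 3.92 × √154 = 0.86.

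**Size of the distortion, with no true age effect.**
- Interval ratio: 63,181.59 / 22,222.73 = 2.84.
- GMT of the pooled adolescents (half at each interval): √(22,222.73 × 63,181.59) = 37,471.
- Apparent ratio, 6-11 to 12-17: 63,181.59 / 37,471 = 1.69, which equals √2.84.

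**How often the planned test would reject.** Simulated lognormal titres with the SDs above, 90 younger children against 60 + 60 adolescents, no age effect:

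| Assumed interval effect in children | Apparent age ratio | Rejection rate |
|---|---|---|
| none | 1.00 | about 5% |
| 1.25-fold | 1.12 | about 14% |
| 1.5-fold | 1.22 | about 33% |
| 2-fold | 1.41 | about 75% |
| 2.84-fold (adult value) | 1.69 | about 97% |

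Limited to the day 112 schedule (90 versus 60), the rejection rate is about 5%, as it should be.

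**Masking.** Suppose the true 6-11 to 12-17 ratio were 1/1.69 = 0.59 and the adult interval effect held. The pooled comparison would reject in about 4% of trials; the day 112 comparison would reject in about 94%.

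**Where the problem does not arise.** Before the boost, interval has not yet had any effect. In Tables 5a to 5d, day 28 post-prime blood is drawn only in Groups 1 and 3, and day 84 and pre-boost day 112 blood only in Groups 2, 3 and 4. Table 1b agrees: adult titres 28 days after dose 1 are 8,734.08 and 8,618.17 in the shortest and longest interval rows, a ratio of 1.01.

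**Late sample.** Day 364 is nominally 364 − 28 = 336 days after the boost in Group 1 and 364 − 112 = 252 days in the others. Pooling there would also mix age with time since boost.

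**The case against.** The strongest objection is that pooling of Groups 1 and 2 is nowhere stated. The one pooling statement, in section 10.1, joins Groups 3 and 4 because they share an interval; by the same reasoning Groups 1 and 2 would stay apart. The protocol calls its methods text brief and defers to a full statistical analysis plan, which may already restrict the contrast. This stands in part. It rules out saying that the analysis will be confounded. It does not clear the wording, because the protocol names the contrast as whole age bands, and the 12-17 band in Table 3 contains both groups. A plan that followed the text would inherit the problem.

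A reader might go further and infer that the age comparison will show a false age effect. The documents do not support that:
- The 97% needs pooling, no true age effect, and the adult 2.84-fold ratio carried over to children. Section 3.2 says the adult intervals varied for logistical reasons, so the ratio is not a randomised estimate.
- The distortion can hide a difference as readily as create one.
- Pre-boost titres and reactions to the first dose are untouched.
- Seroconversion may be near its ceiling: section 3.2 reports neutralising antibody in all 35 adults tested after the booster.
- Table 1b covers antibody only and is no evidence of an interval effect on reactogenicity. Safety is descriptive, untested and already presented by group.

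The simulation also uses all scheduled recipients. The immunogenicity population in section 10.2 needs baseline seronegativity and both doses, section 6.3.6 expects some boosters to be declined, and a footnote to the visit tables appears to give Group 3 participants only one of the last two visits. Actual numbers, and hence rejection rates, would be lower.

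**Conclusion.** The concern holds in a limited form. As worded, the age contrast leaves boost interval uncontrolled for post-boost immunogenicity, and the schedule change made the two bands unequal on interval. The possible distortion is a ratio of about 1.1 to 1.7 for interval effects of 1.25- to 2.84-fold, with false rejection in about 14% to 97% of trials; if children show no interval effect, there is none. This rests on Groups 1 and 2 being pooled, lognormal titres with adult spread, and full scheduled numbers.

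This should be fixed, but it is not critical. It affects one subgroup comparison on secondary endpoints in a trial with no formal primary hypothesis. The age de-escalation and holding rules rest on safety data and do not depend on it. The like-for-like groups already exist in the design.

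**What to change.** Amend the subgroup section, and carry the change into the statistical analysis plan:
- Make the post-boost immunogenicity age comparison within the day 112 schedule (Group 2 versus Groups 3 and 4 combined), or stratify it by boost interval. Report Group 1 separately.
- Make post-prime age comparisons only at shared visits: day 28 for Group 1 versus Group 3; day 84 and pre-boost day 112 for Group 2 versus Groups 3 and 4.

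No new data or visits are needed. The cost is precision, because the adolescent side falls from 120 to 60 ChAdOx1 nCoV-19 recipients. With an SD of ln titre of 0.86, the 95% margin on the ratio is exp(1.96 × 0.86 × √(1/90 + 1/60)) = 1.32-fold either way. With 120 adolescents of the same spread it would be exp(1.96 × 0.86 × √(1/90 + 1/120)) = 1.26-fold. That is a small price for removing a possible 1.7-fold distortion.

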### **10.2. Analysis population**

All participants received at least one dose of study vaccines will be included in the analysis of safety and will be analysed according to vaccine received.

The immunogenicity analyses will include participants who are seronegative to the spike protein at baseline and received both prime and boost vaccine. Sensitivity analyses of immunogenicity data will be conducted including all vaccinated participants regardless of seropositivity status and protocol deviations.

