| Primary
To assess the safety, tolerability and reactogenicity profile of a prime-boost regimen (with an interval between prime and boost of 28 OR 112 days in 12-17 year olds, and interval of 112 days in 6-11 year olds) of the candidate vaccine ChAdOx1 nCoV-19 ( $5.0 \times 10^{10}$ vp / $5.0 \times 10^{10}$ vp) in children aged 6-17 years. | a) occurrence of solicited local reactogenicity signs and symptoms for 7 days following vaccination;
b) occurrence of solicited systemic reactogenicity signs and symptoms for 7 days following vaccination;
c) occurrence of unsolicited adverse events (AEs) for 28 days following vaccination;
d) occurrence of SAEs and disease enhancement episodes
e) occurrence of abnormal laboratory findings (Grade 3 and above) | a)-c) as stated, d) throughout the study, e) D2 and D7 post-boost blood tests (safety bloods) |
| Secondary
To assess cellular and humoral immunogenicity of ChAdOx1 nCoV-19 ( $5.0 \times 10^{10}$ vp / $5.0 \times 10^{10}$ vp) given as homologous prime boost (at 28 and 112 days post prime in 12-17 year olds, and 112 days post prime in children aged 6-11 years)                                                                               | a) Quantify antibodies against SARS-CoV-2 spike protein (seroconversion rates)
b) Virus neutralising antibody (NAb) assays against live and/or pseudotype SARS-CoV-2 virus
c) Interferon-gamma (IFN- $\gamma$ ) enzyme-linked immunospot (ELISpot) responses to SARS-CoV-2 spike protein
d) cell analysis by flow cytometry assays                                                                                            | Blood samples drawn at D0, D28, D56, , D84, D112, D140, D182 and 364                          |

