#### **6.3.6 Declining booster vaccinations**

Following the updated guidance from the MHRA and JCVI on 7th April 2021 regarding the use of ChAdOx1 nCoV-19 in under 30-year olds, it may be expected that some participants or their parents wish to decline a booster vaccination. This should be recorded in the CRF and other study procedures may continue as scheduled. It will not automatically lead to withdrawal from the study unless explicitly stated by the participant or their parent.

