##### 10.1.2. Immunogenicity

Highly skewed ELISA and neutralising antibody data will be log-transformed prior to analysis. The geometric mean concentration (GMC) and associated 95% confidence interval (CI) will be summarised by computing the anti-log of the mean of the log-transformed data.

The GMCs and CIs at day 28 post prime and boost, and the proportion of participants seroconverting (defined as a greater than a four-fold rise) from day 0 to day 28 post boost will be computed.

Spike-specific T cell responses (ELISPOT) will be presented as means and confidence intervals, or medians and interquartile ranges if non-normally distributed at all post vaccination time points.

Comparisons of continuous immunogenicity data between groups or different time points will be made using a Mann Whitney U test because the low titres below detection threshold are expected, which will cause a non-normal distribution. Comparison of seroconversion rates will be conducted using a Chi-squared test.

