### **10.5. Procedure for Accounting for Missing, Unused, and Spurious Data.**

All available data will be included in the analysis.

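### The main immunogenicity population requires the boost at every time point, so post-prime and pre-boost results drop primed children who later miss or decline it

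*Protocol*

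**What the plan says.** Protocol section 10.2 sets the main set without reference to time point: "The immunogenicity analyses will include participants who are seronegative to the spike protein at baseline and received both prime and boost vaccine". It adds one alternative: "Sensitivity analyses of immunogenicity data will be conducted including all vaccinated participants regardless of seropositivity status and protocol deviations".

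Section 10.1.2 plans results from before the boost as well as after it. For antibody it names "The GMCs and CIs at day 28 post prime and boost". For ELISpot it plans means and confidence intervals, "or medians and interquartile ranges if non-normally distributed at all post vaccination time points".

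Tables 5a to 5d place pre-boost immunogenicity bloods at D28 in Groups 1 and 3 and at D84 and D112 in Groups 2, 3 and 4. Groups 2 and 4 have no D28 sample.

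Section 6.3.6 anticipates that, after the April 2021 guidance, "it may be expected that some participants or their parents wish to decline a booster vaccination". It says that this is not in itself withdrawal and that the other study procedures may carry on. Section 6.3.5 says that data and samples obtained before a withdrawal will still be used. Section 5 identifies the children still to be boosted, now at D112, as those in Groups 2, 3 and 4.

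**The concern.** A sample taken before the boost measures the response to the prime alone. Whether the child is boosted afterwards has no bearing on the validity of that sample, yet under section 10.2 it decides whether the sample enters the main analysis. That has two consequences.

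- **Lost precision.** The protocol expects the loss, and the blood will already have been drawn and can be assayed.
- **Selection on a post-baseline event.** Besides refusal, a child may miss the boost through withdrawal (6.3.5), pregnancy (6.3.3, 6.5), a delay or decision after infection (6.3.3), or an individual stopping rule triggered by a persistent related Grade 3 reaction (9.17.2). The last can depend on the vaccine received, so even the ChAdOx1-versus-MenB contrast before the boost is no longer a comparison of the children as randomised.

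The D28 age comparison is conditioned unequally. Group 1 gives its D28 sample at its boost visit. Group 3 gives its D28 sample and is then selected on a boost due at D112, which is 112 − 28 = 84 days later.

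**Working it through.** **The plan's own figure.** No sample size or power is stated for immunogenicity. The only sample-size figure is for safety: with n = 60 and a 5% event rate, 1 − 0.95^60 = 0.954, which agrees with the stated more than 90%. It does not bear on this point.

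**Inputs from the protocol**
- Planned ChAdOx1 recipients: 60 in Group 1, 60 in Group 2, 44 to 46 in Group 3 (Table 3), and 90 in Groups 3 and 4 together (Synopsis).
- Groups with boosts outstanding: 2, 3 and 4, which is 75 + 111 = 186 of 261 participants (71%), or 60 + 90 = 150 of 210 planned ChAdOx1 recipients (71%).

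**Assumption.** The share not boosted, d, is not given. It is set at 10%, 20% and 30%.

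**Loss of precision.** The number retained is n(1 − d). The log-scale confidence interval widens by 1/√(1 − d) − 1.

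| d | Group 3 at D28 (44–46) | Group 2 at D84/D112 (60) | Groups 3+4 at D84/D112 (90) | CI widening |
|---|---|---|---|---|
| 10% | 40–41 | 54 | 81 | 5.4% |
| 20% | 35–37 | 48 | 72 | 11.8% |
| 30% | 31–32 | 42 | 63 | 19.5% |

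These are ChAdOx1 ceilings; baseline seropositivity and missed samples would lower them. The day-28 post-prime GMC, the only pre-boost GMC that section 10.1.2 names, comes from Groups 1 and 3 alone. The 60 and 90 columns therefore apply only at D84 and D112, where ELISpot is planned.

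**In titre units (illustration).** In Table 1b the adult interval at 28 days after dose 1 (under 6 weeks, N = 479) runs from 7,883.1 to 9,676.9. The log SD is ln(9,676.9/7,883.1)/(2 × 1.96) × √479 = 1.145. If children are similarly variable, the interval factor for n = 45 is exp(1.96 × 1.145/√45) = 1.40. With 20% lost (n = 36) it is exp(1.96 × 1.145/√36) = 1.45.

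**Bias.** Let r be the post-prime GMC in non-boosted children divided by that in boosted children. The boosted-only GMC divided by the all-primed GMC is r^(−d).

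| r | d = 10% | d = 20% | d = 30% |
|---|---|---|---|
| 0.5 | 1.072 | 1.149 | 1.231 |
| 1.0 | 1.000 | 1.000 | 1.000 |
| 1.5 | 0.960 | 0.922 | 0.885 |

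The protocol gives no value for r, and even the direction is open. The table shows sensitivity and is not an estimate.

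**Reach of the problem.** After D0, Group 1 is sampled at D28, D56, D182 and D364, and Group 2 at D84, D112, D140 and D364. They share no pre-boost visit. In the younger cohort, section 10.1 combines Groups 3 and 4 because both are boosted at D112.

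**The case against.** **The interval comparison.** A reader might infer that the rule breaks the randomised 28- versus 112-day comparison, because refusals fall mainly in Groups 2 to 4. The documents do not support that for pre-boost results: Groups 1 and 2 have no common pre-boost sample after D0, and Groups 3 and 4 no longer differ in interval. The comparison is made after the boost, where requiring the boost is defensible and the proposed change alters nothing.

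**Section 10.5.** A reader might see a contradiction with "All available data will be included in the analysis". That sentence concerns missing, unused and spurious data and can be read as applying within each defined population. Otherwise it would equally contradict the seronegative restriction. The tension with section 6.3.5, on data from before withdrawal, is closer to the point, although including those data in the sensitivity analysis could be said to honour it.

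**The sensitivity analysis.** It brings prime-only children back, so their data are not lost altogether. The subgroup comparison by baseline antibody status, if run in the all-vaccinated set, would have a non-positive stratum close to the population wanted here. Known seropositivity is also an exclusion criterion, which limits the mixing. This softens the concern. But the sensitivity analysis relaxes serostatus, protocol deviations and boost receipt together, and the protocol does not say in which set the subgroup comparison is run. No stated analysis is limited to baseline-seronegative primed children at pre-boost visits.

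**Blinding and cause.** Participants are blinded, section 6.3.6 ties refusal to policy guidance, infection delays the boost rather than ruling it out, and unblinded children who still lack a second dose are offered completion of their course. All of this makes strong selection less likely, and it stands. It does not restore the precision.

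**Left to the SAP.** The protocol calls its statistical section a brief account, and visit-specific denominators are often set in the SAP. Here, however, the protocol states the population rule and applies it to all immunogenicity analyses.

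**Conclusion.** The point holds for post-prime and pre-boost results only. As written, section 10.2 makes them conditional on a later boost that section 6.3.6 expects some families to decline. The affected results are the day-28 post-prime summaries in Groups 1 and 3, the D84 and D112 results in Groups 2 to 4, the pre-boost ChAdOx1-versus-MenB contrast and the D28 age comparison. The age comparison was never randomised.

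The certain cost is precision, at a size that depends on an unknown rate: intervals about 5%, 12% or 20% wider at an assumed 10%, 20% or 30% not boosted. Bias is possible but not shown; it needs a difference in post-prime response between boosted and non-boosted children, and the documents give none.

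That the loss falls mainly on Groups 2 to 4 is inferred from sections 5 and 6.3.6. The protocol does not state that every Group 1 child had been boosted, and any participant could miss the boost for other reasons. Immunogenicity is a secondary objective, so the primary safety analysis, which includes everyone given at least one dose, is untouched. The change is worth making because the data are already collected and the remedy is small.

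**What to change.** Amend section 10.2 so that the main immunogenicity population is defined by time point:

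- For time points up to and including the pre-boost sample, include all participants who were seronegative to spike at baseline and received the prime.
- For post-boost time points, including seroconversion from day 0 to day 28 post boost, also require receipt of the boost.
- Report the number not boosted in each group.
- Keep the all-vaccinated sensitivity analysis as planned.

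The cost is a short change to the text and denominators that differ by visit, which tables must show and which readers must bear in mind when comparing pre-boost with post-boost values. No visit, sample or procedure changes.
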